##### Immune cell phenotype analysis

2.9.7.2.

Fasting complete blood count and differential will be analyzed in whole blood by fluorescent flow cytometry using an automated hematology analyzer (Sysmex XN10) by Alberta Precision Labs. Immune cell subsets from fresh whole blood are identified in-house by direct immunofluorescence assay. Briefly, 96-well V-bottom plates (Costar^®^, Kennebunk, ME, United States) are pre-conditioned with 200 μL 5% FCS in PBS with AB/AM (IF buffer) for at least 30 min before adding 100 μL of whole blood. The RBCs are lysed using 200 μL of 1X RBC lysis buffer (BioLegend, San Diego, CA, United States). After a 15 min incubation at room temperature, the plate is centrifuged at 402 g for 10 min at 10°C to pellet RBCs. Supernatant is discarded using needle aspiration and RBCs are lysed as previously, incubated for 5–10 min, and plate is centrifuged. If RBC are still evident, a third lyse (5–10 min) will be performed. After RBC lysis, supernatant is discarded and immune cells are washed twice with 200 μL IF buffer and incubated for 30–60 min at 4°C in the dark with a mix of fluorophore conjugated antibodies (except FOXP3) to characterize immune cell phenotypes. The antibodies conjugates, staining reagents, and the corresponding multicolour flow cytometry panels designed to identify immune cell subsets and activation markers [(1) T reg, (2) T cell A, (3) T cell B, (4) B cells, (5) Monocytes, (6) DCs, (7) NK, and (8) T helper] are shown in Supplementary Table S1. After incubation, cells from panels 2–8 are washed twice as previously. Cells are resuspended in 1% paraformaldehyde in PBS for at least 1 hour to fix cells before being transferred to FACS tubes containing 100 μL of IF buffer and stored away from light at 4°C until acquiring. Following the first wash, the Treg cells (panel 1) are resuspended in FoxP3 Fix/Perm solution (Fix/Perm Buffer Set, BioLegend, as above) diluted in PBS, transferred to FACS tubes, and incubated for 20 min at room temperature in the dark for further intracellular FoxP3 staining. Tubes are centrifuged at 428 g for 2 min at 10°C to pellet cells and supernatant is discarded. Cells are washed with FoxP3 Perm buffer solution diluted in PBS and pelleted. After discarding supernatant, cells are resuspended in diluted FoxP3 Perm buffer and incubated, in the dark, at room temperature for 15 min. Cells are pelleted and after discarding supernatant, they are resuspended in 20 μL of anti-FoxP3 antibody mix (diluted with Perm buffer), and incubated at room temperature, in the dark, for 30 min. Cells are washed twice in IF buffer as previously. Cells are resuspended in 300 μL of IF buffer and stored as previously described.

Negative and positive gates are determined using compensation beads (AbC™ Total Antibody Compensation Bead Kit, Thermo Fisher Scientific, as above) to control for fluorochrome spillover. Tandem-specific compensations are employed to account for differences in compensation lot to lot/ vial to vial. Briefly, we label microtubes and FACS tube for each antibody (*n* = 13). Antibodies are diluted in 1:100 μL [BV510, BV421, PerCP, APC, FITC, CD28 (BV711), HLA-DR (BV711)] or 1:200 μL [PE, CD45RO (BV711), CD196 (BV711), CD86 (PECy7), CD185 (PECy7), CD192 (PECy7)] using IF buffer. One drop of positive and one drop of negative beads is added to each FACS tube. 50 μL of previously diluted antibodies are transferred to FACS tubes and mixed with beads. Tubes are incubated at 4°C in the dark for 30 min. IF buffer (200 μL) is added and tubes are centrifuged at 428 g for 2 min at 4°C; 2 min. Supernatant is discarded and wash steps are repeated. Compensations are resuspended in 300–600 μL IF buffer and stored at 4°C await from light. All samples, including compensations, will be acquired within 72 h using a BD LSR-Fortessa X-20 flow cytometer (BD Biosciences, San Jose, CA) and analyzed according to the relative fluorescence intensity using a platform for single-cell flow cytometry analysis (FlowJo 10.8.1, Becton Dickinson & Company). The flow cytometer machine goes through rigorous quality control, including periodical calibration, and is located at the Faculty of Medicine and Dentistry Flow Core at the University of Alberta, which is a recognized laboratory by the International Society for Advancement of Cytometry. Quality control of acquired samples will also be made using a method that adopts algorithms for the detection of anomalous data (flowAI) as previously described (80). Data is processed automatically, with the call of an R function, by optimizing flow rate, signal acquisition, and dynamic range (80). The population of monocytes and lymphocytes (i.e., PMBCs) will be the starting point gate of all immune subsets, which will be determined using established gates based on morphological characteristics of forward and side scatter. Fluorescence minus one (FMO) control will be used to establish positive staining when needed. All analyses are carried out by one individual and gates are reviewed by another to minimize interobserver variability.

##### Immune cell recovery

2.9.7.3.

PBMC cryovials previously stored in liquid nitrogen will be rapidly thawed in a 37°C water bath for 5 min. The cryovials are dried and wiped with 70% ethanol before opening, then PBMCs are transferred to a 9 mL aliquot of 10% FCS RPMI prewarmed at 37°C. PBMCs are spun down and rinsed with 10 mL of 10% FCS RPMI to remove DMSO. PBMCs are resuspended in 5 mL of 10% FCS RPMI and transferred to 12 mL cell culture tubes to rest overnight at 37°C 5% CO_2_. (Forma™ Series II Water Jacket CO_2_ incubator 3,110, Thermo Fisher Scientific, Asheville, NC, United States). Before using in immune assays, PBMCs are pelleted at 453 g for 5 min and resuspended in 2 mL 10% FCS RPMI and lymphocytes counted using the trypan blue (diluted 1:1 with ddH_2_O, Corning, as above) membrane dye exclusion method. All cell counts are carried out by the same person to minimize variation.

##### Mitogen stimulation of PBMC

2.9.7.4.

The quantification of cytokine secretion by PMBCs stimulated with mitogens is used to evaluate the effector function of immune cells. Briefly, PBMCs are cultured in 2 mL 10% FCS RMPI-1640 medium (as above) for 48–72 h at 37°C and 5% CO_2_ without mitogen (unstimulated) or with mitogens. The tubes are set up to reach 1.00 × 10^6^ cells/mL. Depending on the cell recovery, in order of priority, we will stimulate PBMCs with (1) phytohemagglutinin (PHA) (25 μg/mL; Sigma-Aldrich, as above), (2) lipopolysaccharide (LPS) (5 μg/mL; Thermo Fisher Scientific, Carlsbad, CA, United States), (3) pokeweed (PWM) (55 μg/mL;), and (4) phorbol 12-myristate 13-acetate plus ionomycin (PMA + I) (2 μg/mL, Thermo Fisher Scientific, Carlsbad, CA, United States). After incubation, PBMCs are centrifuged at 428 g for 5 min at 18°C to pellet PBMCs. The supernatant is aliquoted and frozen at -80^o^ C for cytokine quantification. The post-pellet fraction is resuspended in 500 μL PBS, transferred to microtubes, and centrifuged at 906 g for 2 min. After discarding the supernatant, the pellet is stored at -80^o^ C for subsequent analysis. All assays are performed with the same number of cells per stimulation and the same concentration of mitogen. For the same participant in both time points we will use mitogens with the same lot number. The incubation time chosen for each mitogen was based off a concentration time course gradient.

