### Study design

2.3.

The NutrIMM study is a prospective, non-randomized, four-arm, parallel-group, unicentre, controlled-feeding trial conducted at the Human Nutrition Research Unit (HNRU), University of Alberta (Edmonton, AB, Canada). A total of one-hundred and twenty-eight participants aged between 18 and 70 years will be assigned with a 1:1 male to female ratio to one of four groups (*n* = 32 per group): Lean-NG, Obese-NG, Obese-GI, Obese-T2D. All participants will be followed up for a total of 4 weeks from the date of group allocation. It will not be possible to blind participants or researchers due to the inclusion specifications of the groups. An overview of the study design is shown in Figure 1.

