##### Cardiometabolic risk factors/ systemic inflammation

2.9.7.1.

Biochemical analysis performed by Alberta Precision Labs includes (1) enzymatic colorimetric assays for triglycerides, total cholesterol, and HDL-C; (2) UV testing using an enzymatic reference method with hexokinase to quantity glucose; (3) an immunoturbidimetric assay for quantification of CRP, all using an automated photometric analyzer (Roche Cobas c503); (4) an electrochemiluminescence immunoassay to determine insulin using an automated immunology analyzer (Roche Cobas e801); and (5) a turbidimetric inhibition immunoassay for hemolyzed whole blood to determine HbA1c using an analyzer designed specifically for HbA1c quantification (Roche Cobas c513). Low-density lipoprotein-cholesterol (LDL-C) is calculated using the following equation: Totalcholesterol−HDLc−(Triglycerides÷2.2). Non-HDL-C is derived from the calculation of total cholesterol minus HDL-C. The Homeostatic Model Assessment for Insulin Resistance (HOMA-IR) index will be calculated using the equation: fasting insulin (microU/L) × fasting glucose (nmol/L)/22.5 (79).

Fasting and post-OGTT levels of circulating cytokines, chemokines, and soluble adhesion molecules will be measured using multiplex assay kits according to the instructions of the manufacturer. All samples will be run in batches with all timepoints per participant on the same plate to minimize variation. Post-OGTT plasma glucose will be measured using a clinical chemistry analyzer (Abbott ARCHITECT c4000, Canon Medical Systems Corporation, Otawara, Tochigi, Japan). The machine is calibrated and compared to controls based off manufacturer recommendations with a CV <5%.

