##### Quantification of *ex-vivo* cytokine secretion

2.9.7.5.

Concentrations of IL-1β, IL-2, IL-6, IL-10, IFN-γ, and TNF-α in the supernatant are determined in duplicate by commercial ELISA kits (DuoSet^®^, R&D Systems, Minneapolis, MN, United States) according to the instructions of the manufacturer. The detection limits for the cytokines are as follows: IL-1β (250 to 3.91 pg/mL), IL-2 (1000–15.6 pg/mL), IL-6 (600–9.38 pg/mL), IL-10 (2000–31.3 pg/mL), IFN-γ (600–9.38 pg/mL), and TNF-α (1000–15.6 pg/mL). Cytokine concentrations are quantified using a microplate reader (Biotek^®^ Synergy™ H1, Agilent Technologies, Inc., Santa Clara, CA, United States), with an intra-assay coefficient of variation <10% and R^2^ of the standard curve ≥0.99. If samples are above the standard curve, they will be diluted onto the linear portion of the standard curve.

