### Confidentiality, data management/monitoring and audit

2.12.

Each participant will be assigned a unique study identifier for use on the case report forms, other trial documents, and the study database. All study records and documents will be treated as confidential and held securely in a locked filing cabinet. These will be retained for at least 5 years. The trial manager will make a separate confidential record of the name, date of birth, unique provincial health care number, phone number, email address, and participant screening number, to permit the identification of all participants enrolled in the study, in case additional follow-up is required. Only the trial manager and principal investigator will have access to the master list of the study that contains identifiable information. Study data are primarily managed using REDCap. All data from clinical visits, excluding data from unredacted source documents, will be uploaded to REDCap and securely maintained by the trial manager in electronic form. Medical information is available through the provincial health information system (Connect Care) and can be assessed by the appropriate medical personnel responsible for the participant’s healthcare. All manually entered data will be double-checked by a different member of the research team for accuracy. In addition, further verification of data will occur through the application of range to confirm if entered values are clinically possible values. Computer held data including the trial database will be held securely and password protected. Access to the study information will be limited to the trial staff and investigators. All collected data obtained as a result of this study is considered confidential and disclosure to third parties is only allowed when required by the ethics committee or regulatory authorities. Currently, there is no institutional quality assurance or scheduled audit procedures at the University of Alberta. Monitoring of the data is carried out by the trial manager as the data is collected at the HNRU. The trial manager is responsible to ensure completeness and accuracy of outcomes, adverse events, group allocations, informed consent, and completion/withdrawal. Access to the trial final dataset will be available to study investigators, trial manager, and graduate students. There are no contractual agreements that limit access to data.

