## Trial status

As of June 16, 2023, the NutrIMM protocol version is 2.1. Enrollment of participants started in October 2019 and will continue until the desired sample size is achieved. Recruitment is expected to be completed in July 2023.

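### Mitogen lot is matched only within a participant and no masking of the IL-2 laboratory work is stated, so the between-group IL-2 comparison is not protected against uneven lot or plate use or an unmasked cell count

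*Protocol article*

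**What the plan says.** All references are to the protocol article.

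- **Lot (2.9.7.4).** "For the same participant in both time points we will use mitogens with the same lot number". No rule is given for lots across participants or groups.
- **Controls that apply to everyone.** Section 2.9.7.4: "All assays are performed with the same number of cells per stimulation and the same concentration of mitogen". Section 2.9.7.3: "All cell counts are carried out by the same person to minimize variation". Section 2.9.7.5 adds duplicate wells, an intra-assay coefficient of variation below 10% and a standard-curve R² of at least 0.99.
- **Plate.** The IL-2 ELISA section (2.9.7.5) has no plate or batch rule. The only same-plate rule is in 2.9.7.1, "All samples will be run in batches with all timepoints per participant on the same plate to minimize variation", and it concerns circulating cytokines, chemokines and adhesion molecules measured by multiplex kits.
- **Blinding (2.3).** "It will not be possible to blind participants or researchers due to the inclusion specifications of the groups".
- **Identifiers (2.12).** "Each participant will be assigned a unique study identifier for use on the case report forms, other trial documents, and the study database". Cryovials are not mentioned.
- **Analysis (2.10).** The first main comparison is an analysis of variance between groups at each time point; the second is a paired test within groups. The adjustment factors named are all participant characteristics.
- **Timing (Trial status).** "Enrollment of participants started in October 2019", with recruitment expected to finish in July 2023.

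**The concern.** The lot rule serves the secondary of the two main comparisons. A shift in IL-2 caused by a mitogen lot cancels in a person's change from baseline to week 4. It does not cancel when groups are compared at one time point, and that is the comparison behind the hypothesis of falling IL-2 from Lean-NG to Obese-T2D. Groups are formed by phenotype, so randomisation does not even out lots or plates between them.

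The reason given for not blinding is that group membership follows from the inclusion criteria. That explains why participants and clinic staff know the group. It does not explain why a person thawing a cryovial, counting cells or reading a plate must know it. The manual trypan-blue count sets the cell number in the IL-2 culture, and the hypothesis has a direction, so an unmasked count is open to expectation.

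If either mechanism operated, its effect on IL-2 could not be told apart from an effect of obesity or glycemia.

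**Working it through.** **1. The plan's own figure.** Section 2.11 gives 32 per group, α = 0.05, power 0.81 and an effect size of 30%. Read as Cohen's f = 0.30 in a four-group ANOVA with N = 128, the noncentrality is f²N = 0.09 × 128 = 11.52. Power is then 0.810, which reproduces the stated figure. The SD scale below rests on this reading.

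**2. Size of the effects the trial looks for.** For four evenly spaced means with step s, the SD of the means is s√1.25. Setting this to 0.30 SD gives s = 0.30/√1.25 = 0.268 SD between adjacent groups. Obese-NG and Obese-T2D, the pair on which section 2.11 bases the effect, are two steps apart: 2 × 0.268 ≈ 0.54 SD. Even spacing is an assumption.

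**3. Bias from uneven lot use.** Bias = lot shift × difference between two groups in the share run on that lot. Neither quantity is in the documents, so both are assumed over a range. Type I error is for a two-sided two-group t-test at 0.05 with 32 per group and no true difference. The SD is inflated for the mixture of lots: SD = √(1 + shift² × mean of p(1−p)), where p is the share on one lot in each group. The noncentrality is (bias/SD) × √(32/2).

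| Lot shift (SD) | Imbalance (points) | Bias (SD) | Type I error |
|---|---|---|---|
| 0.3, 0.5 or 1.0 | 0 | 0 | 0.05 |
| 0.3 | 25 | 0.075 | 0.06 |
| 0.5 | 25 | 0.125 | 0.08 |
| 1.0 | 25 | 0.25 | 0.14 |
| 0.3 | 50 | 0.15 | 0.09 |
| 0.5 | 50 | 0.25 | 0.16 |
| 1.0 | 50 | 0.50 | 0.44 |

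Example for 0.5 SD and 50 points, with shares of 0.75 and 0.25: SD = √(1 + 0.25 × 0.1875) = 1.023, and the noncentrality is (0.25/1.023) × 4 = 0.98.

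**4. If lots are balanced but not modelled.** They only add noise: f becomes 0.30/√(1 + shift²/4). ANOVA power falls from 0.81 to 0.80, 0.78 and 0.71 for shifts of 0.3, 0.5 and 1.0 SD.

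**5. Which outcomes are exposed.** Mitogen lot and the trypan-blue count act on the stimulated-cell assays, IL-2 above all. CRP is measured on an automated analyser at an outside laboratory (2.9.7.1). Flow cytometry stains fresh whole blood, with no mitogen and no trypan-blue count (2.9.7.2).

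**The case against.** The strongest reply is that much of this is laboratory detail. Plate layout, run order and vial coding belong in operating procedures, and a lot term belongs in the analysis plan that section 2.10 promises. An article need not print either. That is fair, and their absence alone would be no finding. What remains is what the article does state: a lot rule set at the level of the participant, in an otherwise very detailed laboratory section, and a blanket blinding statement whose reason does not cover the laboratory.

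A reader might infer more, and the documents do not support it:

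- *That assay control protects only the within-person comparison.* The single counter, the fixed cell number and mitogen concentration, and the ELISA limits apply to all groups. With one counter, differences between operators cannot line up with group; only expectation remains. The ELISA limits quoted do not, however, bound plate-to-plate differences.
- *That lots were in fact aligned with group.* Nothing says that groups filled at different speeds, that vials are run in enrolment order, or that several lots were used. The matching rule suggests only that more than one lot was foreseen.
- *That laboratory staff knew the group.* Section 2.3 does not name them. The study identifier may give some masking, though none is claimed.
- *That the same-plate rule covers IL-2.* It is written for a different assay.
- *That flow results share the problem.* The mechanisms do not reach them. Established gates, fluorescence-minus-one controls where needed, automated quality control and review by a second person already limit gating bias.

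**Conclusion.** The concern holds in a limited form. As written, the primary between-group IL-2 contrast is not protected against uneven lot or plate use, or against expectation in an unmasked count. Bias is possible, not shown.

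Its size cannot be taken from the documents. With an assumed 0.5 SD lot effect it runs from zero under balanced use to 0.25 SD at a 50-point imbalance. The upper value is close to the 0.268 SD step between adjacent groups, but under half of the roughly 0.54 SD between Obese-NG and Obese-T2D (0.25/0.54 = 0.46). Judging it against the adjacent step alone would overstate it. These comparisons assume f = 0.30 and even spacing. No figure can be put on expectation bias in the count. CRP, the other primary outcome, is not affected.

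**What to change.** - **IL-2 assays not yet run.** Thaw, stimulate and plate in blocks that each hold participants from all four groups, with both time points of a participant together on one lot. Code the vials so that those who count, stimulate and read do not know the group. The cells are cryopreserved, so run order can still be chosen.
- **IL-2 assays already run.** Report lot and plate by group, and include lot/run as a term in the IL-2 model, fixed if there are few lots.
- **Section 2.3.** Limit the statement to participants and clinic staff. State laboratory masking only for work that was actually done masked.
- **Flow cytometry.** Only masked gating of the remaining analyses applies; fresh samples cannot be reordered.

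The cost is some ordering and labelling work and a few degrees of freedom. In completed assays, a lot effect fully aligned with group cannot be removed by any model; it can only be disclosed.

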##### Quantification of *ex-vivo* cytokine secretion

2.9.7.5.

Concentrations of IL-1β, IL-2, IL-6, IL-10, IFN-γ, and TNF-α in the supernatant are determined in duplicate by commercial ELISA kits (DuoSet^®^, R&D Systems, Minneapolis, MN, United States) according to the instructions of the manufacturer. The detection limits for the cytokines are as follows: IL-1β (250 to 3.91 pg/mL), IL-2 (1000–15.6 pg/mL), IL-6 (600–9.38 pg/mL), IL-10 (2000–31.3 pg/mL), IFN-γ (600–9.38 pg/mL), and TNF-α (1000–15.6 pg/mL). Cytokine concentrations are quantified using a microplate reader (Biotek^®^ Synergy™ H1, Agilent Technologies, Inc., Santa Clara, CA, United States), with an intra-assay coefficient of variation <10% and R^2^ of the standard curve ≥0.99. If samples are above the standard curve, they will be diluted onto the linear portion of the standard curve.

##### Proliferation assay

2.9.7.6.

The proliferation of T cells will be measured at baseline and after the intervention period using the fluorescence of a cell viability reagent (alamarBlue^®^ BUF012A, Bio-Rad Laboratories, Hercules, CA, United States). PBMCs are stimulated with anti-CD3 and anti-CD28 (BioLegend, as above). Briefly, black flat bottom 96-well cell culture plates (NUNC^®^, Thermo Fisher Scientific, Roskilde, Copenhagen, Denmark) are coated with 100 μL of 5 μg/mL anti-CD3 stock solution and are incubated overnight at 4°C. Then, stock solution is discarded using needle aspiration and rinsed twice with 200 μL sterile PBS. For the unstimulated and stimulated wells, 200 μL and 196 μL of 10% RPMI is added, respectively. The plate is set up to reach 1.00 × 10^6^ cells/mL in 200 μL. Samples are added in triplicate, with 4 μL of 50ug/mL anti-CD28 (previously diluted 10X in 10% RPMI) stimulation of coated CD3 wells. Plates are incubated at 37°C with 5% CO_2_ for 68 h. After 68 h, alamar blue is added equal to 10% of total volume (22.2 μL) and cells are incubated for 4 more hours for a total of 72 h. The plate is excited at 560 nm in a fluorescent microplate reader (Biotek^®^ Synergy™ H1, as above) and read at 590 nm. Data is expressed as arbitrary units/OD 590 nm, using individual values or delta.

